### Harms

3.5

Adverse events (expected), unexpected adverse events (UAE), and serious adverse events will all be described using a detailed documentation form and logged in the Research Electronic Data Capture (REDCap) [46,47] system to be summarized and reported to the institutional IRB and with future publications. Expected adverse events described in consent documentation include mental health exacerbations or triggers associated with meditation and/or completing self-report questions as well as scrapes or allergic reactions associated with sEMG procedures.

### Outcome measures

3.6

Instruments used include a battery of self-reported questionnaires for demographics, health history, pain, physical function, quality of life (QoL), depression, and mindfulness; an additional and objective measure of physical function is sEMG recording collected baseline and follow-up visits. Questionnaires are completed using the REDCap online data management platform. MBI + TAU participants are asked to complete a daily practice log with their VAS to track their mindfulness practice in minutes.

*Demographic and personal contact Questionnaire:* In addition to common demographic characteristics, this questionnaire asks participants to report their primary clinic for treatment of LR. Participants are also asked to provide the screen name they are using to log into video conferencing for synchronous sessions.

*Lumbosacral Radiculopathy/Radiculitis Health History Questionnaire:* This questionnaire, developed by the study team, collects information on the duration of patient's symptoms, current and previous treatments including duration, and the perceived effectiveness of previously attempted treatments.

*Modified Oswestry Low Back Pain Disability Questionnaire/Oswestry Disability Index (ODI):* The ODI is designed to assess the intensity of pain and the degree to which pain interferes with activities of daily living such as personal care, lifting, walking, sitting, etc. The ODI has been found to have high sensitivity, specificity, validity, and test-retest reliability for patients with low back pain [[48], [49], [50], [51], [52], [53]].

*Visual Analog Scale (VAS)*: The VAS is a self-reporting scale where participants are asked to report their pain on a scale from 0 to 10 where 0 represents “no pain” and 10 represents “worst pain.” The VAS has been used in many pain intervention studies and has shown to have high reliability, validity, specificity, and sensitivity [51,54,55]. The VAS has established validity and reliability and has been used to establish a minimum clinically important difference and a minimum detectable change for other pain questionnaires [56,57].

*painDETECT Questionnaire (PD-Q):* The PD-Q is a self-reporting pain questionnaire that is designed to assess the presence of neuropathic pain in patients with chronic low back pain and lumbosacral radiculopathy/radiculitis. The PD-Q is scored on a scale from −1 to 38 where scores 19 or greater indicate likely presence of neuropathic pain, scores from 12 to 18 represent ambiguous pain, and scores below 12 represent a likelihood that neuropathic pain is not present. The PD-Q has been found to have high sensitivity, specificity, validity, and test-retest reliability in patients with low back pain and lumbosacral radiculopathy/radiculitis [4,[58], [59], [60], [61], [62]].

*SF-12 Patient Questionnaire for Quality of Life (SF-12 QoL):* The SF-12 QoL assesses an individual's overall quality of life using self-reporting questions to determine an individual's ability to accomplish and complete activities of daily living as well as their overall mood and outlook on life [63]. The SF-12 has been found to have acceptable reliability and validity and has been recommended as a useful alternative to the SF-36 if questionnaire length is a concern [51,[63], [64], [65]].

*Major Depression Inventory (MDI):* The MDI is a self-reporting questionnaire that includes questions about depression symptoms consistent with the *DSM-V* guidelines for major depressive disorder. The MDI is commonly used in research to determine the degree to which an individual is currently experiencing a depressed mood and has shown to have high sensitivity, specificity, validity, and test-retest reliability for patients with low back pain [66,67]. Participants who score above a 30, indicating severe depression symptoms, will be sent a referral for medical management.

*Five Facet Mindfulness Questionnaire (FFMQ):* The FFMQ is a self-reporting questionnaire that assesses an individual's trait mindfulness using five “facets” or categories of mindfulness: Observing, Describing, Acting with Awareness, Nonjudging of inner experience, and Nonreactivity to inner experience. Participants respond to 39 questions such as, “I can easily put my beliefs, opinions, and expectations into words”, on a scale of never or very rarely true (1) to very often or always true (5). The FFMQ has demonstrated good construct, discriminant, and predictive validity, as well as its internal consistency and correlation with negative affective symptoms [[68], [69], [70], [71]].

*Mindful Reinterpretation of Pain Sensations (MRPS) scale:* The MRPS is a 9-item survey that asks participants to rate their level of agreement with statements such as “I try to watch my pain from a distance, as if I were an objective observer,” and “I “zoom in” close to the pain to see what sensations it is made up of” on a scale ranging from, “never do that”, (0) to, “always do that”. (6). The MRPS scale was designed by [name], the developer of MORE, based on the reinterpretation component of the Coping Strategies Questionnaire [72]. The MRPS scale is currently pending validity publications but is preliminarily reported to have high sensitivity to the effects of MORE.

*Surface Electromyography (sEMG):* Participants undergo sEMG to evaluate the function of the anterior tibialis and lateral gastrocnemius muscles, which have been shown to be dysfunctional in patients with L5 and S1 nerve root compression [8,9,73]. For administration of sEMG, study personnel utilize Thought Technologies sEMG Equipment: ProComp Infiniti System with BioGraph Infiniti Software (Model #T7500 M), EMG MyoScan-Z Sensor (Model#: T9503Z, 2048 samples/second), EMG Myoscan-Pro Sensor (Model#: T9401M-60, 256 samples/second), and the Tele-Infinit Compact Flash (Model#: T9600) for wireless communication of sEMG data. The MyoScan-Z Sensors are be placed on the lateral gastrocnemius of both legs, as this muscle is more commonly affected in LR and a valuable target for high sampling rate diagnostic equipment. Root mean square (RMS), a component derived from an sEMG wave, represents the force/torque produced by muscles [74], measured in microvolts, and correlates with weaker contractions in the presence of chronic pain. [[75], [76], [77], [78]], while RMS peak time represents the time during the gait cycle at which RMS was highest. These two variables will be used for analysis of physical function as previously studied [9]. Fig. 2 depicts the placement of sEMG electrodes.

**Fig. 2 fig2:**
[figure not shown]
sEMG Sensor and Electrode Placement [73].

### Power and sample size calculations

3.7

Using results of Braden et al., a standard deviation of 8.3 points for the Oswestry Disability Index was used for effectiveness of mindfulness-based stress reduction in LBP patients [79]. An effect size of Cohen's *d* = 0.83 was calculated when using the reported minimal clinically important difference of a 10-point change [57,80]. Effect sizes ranging from 0.5 to 1.1 have been found previously for mindfulness interventions using outcome measures of pain and physical function in mechanically and neurologically derived LBP. The large effect sizes powered for in this study are considered acceptable due to the large effect sizes found in studies using MORE with multiple outcomes measures [35,36,41]. Using the GPower program (version 3.1.9.4) for *a priori t*-test sample size calculations using *alpha* = .05 yields 80% power to detect an effect of treatment of size *d* = 0.83, with a sample size of 48 participants. When adjusting for an expected retention rate of 80%, a total proposed sample size of 60 participants is required (*n* = 30 per group).

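### The planning effect size of 0.83 does not follow from a 10-point difference and an SD of 8.3 (10/8.3 = 1.20); it equals the inverse ratio, so the 80% power does not belong to 10 ODI points

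*Protocol article*

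**What the plan says.** Section 3.7 (Power and sample size calculations) of the protocol article builds the sample size in four steps.

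- Variability: "a standard deviation of 8.3 points for the Oswestry Disability Index was used", taken from an earlier study of mindfulness-based stress reduction in low back pain.
- Effect size: Cohen's d = 0.83, which "was calculated when using the reported minimal clinically important difference of a 10-point change".
- Sample size: a t-test calculation in GPower at alpha .05 gives "80% power to detect an effect of treatment of size *d* = 0.83", "with a sample size of 48 participants".
- Retention: 80% is expected, which raises the total to 60, or 30 per group.

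The section also supports the planning value by citing effects of 0.5 to 1.1 in earlier mindfulness trials, and large effects in studies of MORE. It gives no second SD, no correlation between baseline and follow-up, and no variance adjustment.

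**The concern.** A standardised effect is the difference divided by the standard deviation. When the difference (10) is larger than the SD (8.3), d must exceed 1. A value of 0.83 cannot come from these inputs, and it coincides with the SD divided by the difference.

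This is the only sample size rationale in the article. A reader who follows it will conclude that the trial has 80% power for the minimal clinically important difference of 10 ODI points. If the SD is right, the design can detect a clearly smaller difference at that power. If the SD is wrong, the power for 10 points is unknown until the correct value is found. The article does not let the reader tell which case applies.

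**Working it through.** **Inputs, all from section 3.7.** SD 8.3; difference 10; stated d 0.83; alpha .05; power 80%; 48 analysed (24 per group); retention 80%; 60 enrolled (30 per group). Sidedness is not stated. I use two-sided, because at d = 0.83 a one-sided test needs 19 per group (38 in total), not 48.

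**Formulae.** d = difference/SD. With n per group, the noncentrality is d × √(n/2) on 2n − 2 degrees of freedom. Power is the probability that the noncentral t variable falls beyond the two-sided 5% critical value.

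**1. Reproduce the plan's figures from d = 0.83.**

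- n = 23: power 78.6%.
- n = 24: noncentrality 0.83 × √12 = 2.875 on 46 df; power 80.4%.
- So 24 per group, 48 in total, and 48/0.80 = 60.

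Every step after d is correct. The fault is in d or in the inputs it was calculated from.

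**2. Check d.**

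- Difference/SD: 10/8.3 = 1.205.
- SD/difference: 8.3/10 = 0.830.

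The printed value matches the second ratio exactly. The first is 45% larger (1.205/0.83 = 1.45), so rounding cannot explain the gap.

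**3. Could a change-score SD explain it?** If 8.3 were the SD at a single time point, the SD of change would be 8.3 × √(2(1 − r)), where r is the correlation between baseline and follow-up. Then:

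| r | SD of change | d for 10 points |
|---|---|---|
| 0 | 11.74 | 0.85 |
| 0.25 | 10.17 | 0.98 |
| 0.5 | 8.30 | 1.20 |
| 0.7 | 6.43 | 1.56 |

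No r of zero or more brings d down to 0.83.

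**4. What the design delivers on the stated inputs (SD 8.3).**

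- d = 0.83 corresponds to 0.83 × 8.3 = 6.9 ODI points.
- Power for 10 points with 24 per group: noncentrality 1.205 × √12 = 4.17; power 98.3%. With all 60 participants it is 99.6%.
- Sample size for 80% power at 10 points: 11 per group gives 76.7% and 12 gives 80.5%, so 24 analysed and 24/0.80 = 30 enrolled.

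**5. What SD would make the text true?** 10/0.83 = 12.05.

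**6. Power for 10 points with 48 analysed if the SD is not 8.3.** The SDs from 10 to 16 are assumed for illustration and do not come from the article.

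| SD | d | Power |
|---|---|---|
| 8.3 | 1.20 | 98% |
| 10 | 1.00 | 92% |
| 12 | 0.83 | 81% |
| 14 | 0.71 | 68% |
| 16 | 0.63 | 56% |

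**The case against.** The inconsistency itself cannot be defended, but several limits on its meaning can be argued.

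- **The cause is inferred.** The article shows no division. An SD misread or mislabelled from the source would produce the same conflict. This stands: what is proved is that the three figures cannot all hold. The exact match with 8.3/10 makes inversion the likeliest cause, not a certain one.
- **The power sentence is literally correct.** The 80% is attached to d = 0.83, and at that d it is right. True, but the preceding text derives that d from the 10-point difference, so the reader is led to attach the 80% to 10 points.
- **The error is conservative.** On the stated inputs the trial has more power for 10 points than claimed. This stands, with the condition that the SD really is 8.3. Above about 12, power for 10 points falls below 80%.
- **The appeal to earlier effects still fits.** The trial was sized on 0.83, which lies within 0.5 to 1.1. That is fair for the design as sized. It does not fit the stated target: 10 points at SD 8.3 is d = 1.20, above that range.
- **The analysis is untouched.** What a result excludes is set by its confidence interval, not by the planning d. This also stands; the damage is to the justification of the sample size.

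The condensed format of an article is no answer. The inputs and the result are printed together and disagree, which is a contradiction, not an omission.

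**Conclusion.** The concern holds. SD 8.3, a 10-point difference and d = 0.83 are mutually inconsistent, and nothing else in the article reconciles them. Assuming a two-sided t-test with equal groups and 48 analysed, one of two statements is true:

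- the SD is 8.3, and the 80% power refers to about 6.9 points, roughly 3 points below the stated target; or
- the SD is about 12.05, and the printed 8.3 is wrong.

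The sample size is not shown to be too small, and the later arithmetic is sound. The correction is nonetheless necessary, because the article's sole sample size rationale rests on a miscalculated figure and tells the reader the wrong detectable difference.

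**What to change.** Check the ODI standard deviation in the cited source first, then correct section 3.7 in one of two ways.

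- **If 8.3 is right:** state d = 10/8.3 = 1.20. Say that 48 analysed participants give about 98% power for 10 ODI points, and 80% power for d = 0.83, which is 6.9 points. Give a reason for keeping 60, since 30 enrolled would meet 80% power for 10 points. A wish to detect differences smaller than 10 points, or caution about the SD, would serve if that was the intention. Note that 1.20 lies above the 0.5 to 1.1 range cited in the same section, and adjust that argument.
- **If the SD is about 12:** correct the SD and leave d, 48 and 60 as they are.

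In either case, state that the test is two-sided. It would also help, though it is not essential, to say whether the SD is of the score or of the change, and to give power over a labelled range of SDs such as the table above.

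The cost is one rewritten paragraph. Enrolment, analysis and conduct do not change.

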### Statistical analytical plan

3.8

Participant descriptive information collected at baseline, including demographics, pain characteristics, physical function, QoL, depression, and trait mindfulness will be reported as mean (SD) or number (percent), as appropriate, for each study group. Likewise, changes from baseline to follow-up of each outcome measure will be reported as mean (SD) for each group.

*A priori* analytical modeling has been developed based on primary and secondary outcome measures and established relevant covariates. Relevant covariates (according to priority) include age, sex [7], change in treatment during study enrollment (as a binary variable), disease etiology [81,82], duration of symptoms prior to study enrollment, previous condition specific surgery [81], and baseline instrument score. To retain adequate power for linear mixed modeling, only covariates that are correlated to the outcome measure of interest (*r* ≥ .3, by Pearson or point-biserial correlation, as appropriate) will be retained. Covariates found to be significantly correlated will be added to the relevant model in a stepwise fashion in the aforementioned order.

All outcome variables aside from VAS pain (pain severity, physical function, QoL, depression symptoms, trait mindfulness, and reinterpretation of pain) will be analyzed using linear mixed modeling with maximum likelihood estimation of missing data to compare mean change between the MBI + TAU and TAU groups’. Next, we will evaluate associations between pain, physical function, QoL, depression symptoms, trait mindfulness, and reinterpretation of pain in relation to time spent practicing mindfulness amongst participants in the intervention group. The same approach will evaluate for significant differences in RMS and RMS-peak time within sEMG findings from baseline to follow-up. Finally, we will evaluate the association between changes in RMS from baseline to follow-up and change scores of the ODI, VAS, and PD-Q in participants in the intervention group.

For all models, we will complete a modified intention-to-treat analysis (mITT) including all those participants who completed the program. A per-protocol structure using only those participants in the treatment group who completed a minimum of 5 sessions synchronously will be used for sensitivity analysis as has been used previously in clinical trials and trials of MORE [41,83,84].

Evaluation of daily VAS scores will be conducted using growth curve analysis with day 1 of the intervention for the respective cohort as the intercept to account for changes in VAS occurring between baseline and intervention initiation.

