### Study design

3.2

Baseline visits conducted at Helfgott Research Institute include confirmation of eligibility criteria, informed consent, study questionnaires, and sEMG collection for 20 gait cycles. Follow-up visits include all steps except repeated informed consent. All participants receive an email containing the informed consent document after baseline visit. Within 16 weeks of baseline visit completion, participants are randomized to either an 8-week MBI and treatment as usual (MBI + TAU) or TAU-only group to be completed in parallel cohorts. Both groups are asked to refrain from changes to their current treatment plan whenever reasonable (i.e., to avoid self-directed changes in treatment such as starting a new supplement) and to report any medically necessary (i.e., physician-recommended or -implemented) changes made during study enrollment. All study participants receive a copy of a pain education handout, “Understanding Pain,” at the time of intervention initiation as an effort to reduce the disparity upon health education [42]. This handout is provided publicly by the Oregon Pain Management Commission. Participants in both groups are asked to report daily pain levels using a Visual Analog Scale (VAS) administered via text message or email as preferred per participant.

Treatment as usual was chosen as the control condition for this experiment, as experts recommend using TAU control groups in studies of MBIs based on evidence from other RCTs conducted in this realm [43]. MORE has not been studied in the context of LR, and no gold standard has been identified as an active control for MORE in this subpopulation; therefore, TAU was deemed as appropriate for this study design. The control group undergoes TAU over 8 weeks of parallel group comparison and starts their 8-week enrollment period on the same day as the experimental group. Participants assigned to the TAU control group are offered to join a MORE program be delivered after the data collection period of the trial has ended. Our study team offered this option as we anticipate a benefit from MORE in the management of lumbosacral radiculopathy. A study flowchart can be seen in Fig. 1.

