### Randomization and blinding

3.3

Cohorts of 24–46 (12–23 per group) participants are recruited into the study and undergo group assignment via simple randomization using a random number generator. Enrollment concludes at their follow-up visit within 6 weeks after the end of their 8-week reporting (intervention) period. To conserve scientific integrity and minimize the introduction of researcher bias, research assistants conducting study visits are blinded to participant group assignment (single-blind). Allocation concealment is maintained by limiting access to the random sequence until the moment of assignment, and a new random sequence is generated for each cohort. Randomization assignment is completed by the study coordinator using a list of anonymized study IDs for that cohort. To prevent experimenter bias, research staff providing the intervention will not be allowed to run follow-up study visits for participants in any cohort to which they have delivered an intervention. Participants unable or unwilling to complete an in-person follow-up visit are provided with the option to complete the questionnaires virtually; this policy was implemented to optimize retention given the ongoing global pandemic and anticipated challenges with in-person follow-up visits.

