To maintain anonymity, participants chose a “screen name” at their baseline study visit that is associated with them at session log in and participants were encouraged, not required, to participate in group discussion using their camera and microphone. Participants in the intervention group complete weekly activities and daily guided mindfulness practices via pre-recorded MP3 files at home consistent with the MORE protocol [34]. Audio from the synchronous sessions is recorded and stored securely for participants absent from synchronous sessions. Participants who do not attend sessions without providing advance notice to the study team will be contacted using the combination of communication methods to which they indicated they preferred at the baseline visit (i.e. phone, text, or e-mail). Attempts to contact the participant will be made until the participant has reached the maximum allowed number of missed sessions, at which point they will be declared lost to follow up. In addition to completing a daily VAS and reporting treatment changes, MORE participants are also asked to report their daily time spent practicing mindfulness. All adverse events occurring during the study, including those observed by or reported to the research team, will be recorded.

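### Treatment change during enrolment, recorded largely after randomisation, is a listed covariate for the between-arm models and can distort the estimated effect of MORE

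*Protocol article*

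**What the plan says.** Section 3.8 (Statistical analytical plan) plans linear mixed models "to compare mean change between the MBI + TAU and TAU groups" and gives a ranked covariate list that begins: "Relevant covariates (according to priority) include age, sex [7], change in treatment during study enrollment (as a binary variable". The list continues with etiology, symptom duration before enrolment, previous surgery and, last, the baseline score. To protect power, it retains "only covariates that are correlated to the outcome measure of interest", with r ≥ .3 as the threshold, and then: "Covariates found to be significantly correlated will be added to the relevant model in a stepwise fashion in the aforementioned order".

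Three other sections show when the variable arises:

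- Section 3.2 (Study design) asks both groups "to report any medically necessary (i.e., physician-recommended or -implemented) changes made during study enrollment". It also sets the timing of allocation: "Within 16 weeks of baseline visit completion, participants are randomized".
- Section 3.4 (Intervention) places the reporting within the intervention period: "In addition to completing a daily VAS and reporting treatment changes, MORE participants are also asked to report their daily time spent practicing mindfulness".
- Section 3.3 (Randomization and blinding) sets the end of the window: "Enrollment concludes at their follow-up visit within 6 weeks after the end of their 8-week reporting (intervention) period".

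Nowhere does the article limit the variable to changes made before randomisation, confine it to a sensitivity analysis, or give it a mediation purpose.

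**The concern.** The other six covariates are fixed before allocation. This one is mostly determined afterwards. The changes that participants may make are those a physician recommends, which plausibly follow worsening symptoms, and the trial's hypothesis is that MORE improves symptoms. On that hypothesis allocation can alter the rate of treatment change, and treatment change shares causes with the outcome. Conditioning on it can remove part of the effect of MORE (a mediator) and can also compare arms within groups that randomisation did not form (a collider).

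The screen adds to this. It admits the variable when its correlation with the outcome is high, which is where the distortion is largest for a given difference in rates. The variable could enter some outcome models and not others, so the reported effects would not all estimate the same quantity. It also ranks ahead of the baseline score, a pre-randomisation covariate.

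**Working it through.** **Inputs from the article.** d = 0.83, taken as stated; ODI SD 8.3; alpha .05; 80% power; 48 evaluable and 60 in total (section 3.7); screen r ≥ .3 (section 3.8), read here as an absolute value.

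**Inputs assumed, because the article gives none.** Rates of treatment change, their correlation with outcome, and a baseline–follow-up correlation of 0.5. Outcomes are in SD units, positive meaning benefit.

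**1. The plan's own figure.** A two-sided, two-sample t-test at d = 0.83 needs 24 per arm (power 0.804), so 48; 48/0.80 = 60. Both figures reproduce, and this point does not alter them.

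**2. Formula.** In a linear model with one outcome per person,

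adjusted effect = unadjusted effect − β × (p_MORE − p_TAU),

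where p is the proportion changing treatment and β is the within-arm outcome difference, changers minus non-changers. If the rates are equal, the shift is zero. If MORE raises the rate, its sign reverses.

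If treatment changes when a latent variable with correlation −0.5 with outcome crosses a threshold, and the arms are of equal size,

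β = −0.5 × [φ(z_TAU) + φ(z_MORE)] / [p_TAU(1 − p_TAU) + p_MORE(1 − p_MORE)].

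**3. Single-outcome results.**

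- (a) No true effect, 40% versus 20%: β = −0.5 × (0.386 + 0.280)/(0.24 + 0.16) = −0.833. Adjusted effect = 0 − (−0.833)(−0.20) = −0.167. Simulation gave −0.16 to −0.17.
- (b) True effect 0.83, which itself lowers changes from 34.8% to 21.1%: β = −0.5 × (0.370 + 0.289)/(0.227 + 0.166) = −0.84. Adjusted effect = 0.83 − 0.84 × 0.137 = 0.715. Simulation gave 0.71–0.72, a loss of about 13–14%.
- (c) As (a) with the rates reversed, 20% versus 40%: 0 − (−0.833)(+0.20) = +0.167, in favour of MORE.

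For latent correlations of 0.3–0.6 the shift is 0.10–0.20 SD in (a) and 6–19% in (b). At 0.3 the correlation with outcome is only about 0.22–0.25, so the variable would usually fail the screen.

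**4. Change-score and baseline-adjusted forms.** If treatment change follows the follow-up level, its latent covariance with the change score is −0.5 × (1 − 0.5) = −0.25, and the SD of change is √(2 − 2 × 0.5) = 1. The shift therefore halves, to 0.167/2 ≈ 0.08 in (a) and 0.115/2 ≈ 0.06 in (b); simulation gave 0.09 and 0.06. If it follows the change score directly, the full figures of step 3 return. A baseline-adjusted model lies within this range. Overall that is 0.06–0.17 SD: 0.06 × 8.3 = 0.5 and 0.17 × 8.3 = 1.4 ODI points.

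**5. The screen.** Where treatment change tracks the modelled outcome directly, the correlation in (a) is about 0.36–0.37 and passes. Where it tracks the follow-up level but is screened against change, the correlation is 0.18 in (a) and 0.23 in (b), below the threshold on average.

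**6. Baseline/follow-up mixed model.** With both visits observed, the arm-by-time term is the between-arm difference in mean within-person change. A time-constant main effect cancels from within-person differences. In fitted examples with 48 participants the estimate did not move (1.2308 and 1.2308). It moved only when a covariate-by-time term was added (1.250 to 1.185; 1.379 to 1.160).

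**7. At the planned size.** A separate single-outcome simulation, with 24 per arm, the screen applied and a true effect of 0.83, used a moderate and a strong setting in which MORE lowers treatment changes and an unmeasured worsening course raises them. The variable was retained in 51% and 76% of trials, the mean estimate was 0.75 and 0.68, and power fell from about 0.80 to 0.73 and 0.65. With no true effect, the type I error was 0.053 and 0.070. With a true effect and no influence of MORE on treatment change, the large-sample adjusted and unadjusted effects were both 0.83.

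**The case against.** The strongest objection concerns the model. The plan is a mixed model of mean change, and the article mentions no covariate-by-time interaction. Step 6 shows that a main effect then leaves the arm-by-time term untouched when pairs are complete. This stands, and it rules out a reading that a reader might infer, namely that listing the covariate necessarily biases the MORE effect. It does not dispose of the point. The article does not fix the specification, and listing the baseline score as a covariate suggests a change-score or baseline-adjusted form, in which bias can arise.

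The assumed rates have no documentary support. Participants must be willing to avoid unnecessary changes (Table 1), and both arms are asked to refrain, so true rates may be lower or equal across arms. Scenario (a) also supposes that MORE halves treatment changes without affecting the outcome, which sits apart from the symptom-driven mechanism. These objections limit the size. They do not remove the physician-led changes, which are the ones most likely to follow symptoms.

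Bias against MORE might be called conservative. That holds only if MORE lowers treatment changes; if weekly contact or greater awareness raised them, the sign would reverse. Some changes may also precede randomisation, given the interval of up to 16 weeks, but the variable as defined mixes these with later ones.

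Finally, this is not a detail left to an unseen analysis plan. The article names the covariate, its rank and its entry rule.

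**Conclusion.** The point holds in conditional form. The article names a variable recorded largely after randomisation as a covariate for the between-arm models. If it passes the screen and enters a change-score or baseline-adjusted model, or enters with a time interaction, the adjusted arm effect does not estimate the total randomised effect whenever allocation affects treatment change and treatment change is related to outcome within arms. Under the assumed rates and a latent correlation of 0.5 the bias is about 0.06–0.17 SD, with its direction set by whether MORE lowers or raises treatment changes. The documents fix neither the size nor the direction.

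A reader might also infer that the comparison is unbiased once the covariate is gone. The documents do not support that: section 3.8 limits the modified intention-to-treat set to those who completed the programme, which is itself selection after randomisation.

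**What to change.** Delete treatment change during enrolment from the covariate list of every between-arm model and adjust only for variables fixed before randomisation. Report treatment changes by arm descriptively. If a model adjusted for them is wanted, label it supplementary and say that it does not estimate the total effect of assignment to MORE.

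The cost is one item removed from a list and one descriptive table. It needs no new data, leaves 48 evaluable and 60 in total unchanged, and touches no rule on patient care. It removes this source of bias only; the completer-based analysis set needs separate attention.
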